**Fig 4 pone.0340593.g004:**
[figure not shown]
Area task: We illustrate two given trials over time (t) in which A. the foveal circle’s size starts smaller than the peripheral one and B. the foveal circle size starts larger than the peripheral one. Participants’ task is to adjust the foveal circle’s area to match the peripheral circle area. In all cases participants report their final size selection with a mouse click. The size of the fixation cross is randomised between trials to prevent local cues from biasing participants’ responses. Note that while we represent the stimuli in black and white here, the real task will involve coloured stimuli and will be performed with the coloured glasses as shown in Fig 1A. This will allow us to present the stimuli either to the contralateral eye or ipsilateral eye.

Peripheral circles will always be of fixed diameter, which will depend on each participant’s blind spot size and padding (peripheral diameter = participant’s blind spot size along longest dimension + 1.5 DVA of padding). The starting size of the foveal circle for a given trial will be randomly sampled from a distribution of smaller (5 values subtracted from the peripheral circle diameter in steps of peripheral circle diameter/10) and larger sizes (5 values added to the peripheral circle diameter in steps of peripheral circle diameter/10) with respect to the peripheral circle size. Fixation size will be adjusted by the participant by scrolling their mouse up (foveal circle diameter + peripheral circle diameter/10) or down (foveal circle diameter – peripheral circle diameter/10). Troxler’s fading occurs when an unchanging peripheral stimulus is experienced to disappear as a participant fixates centrally ([27,28]). To minimise this illusion, the peripheral circles will be dashed (12 dashes each spanning 15 degrees, and with a gap of 15 degrees between adjacent dashes) and will alternate between two orientations about its centre, by a polar angle of 15 deg, back and forth every 366ms.

For each trial, the circle stimuli (foveal and peripheral) will be presented dichoptically either to the contralateral or the ipsilateral eye, while the fixation cross and fusion stimuli will be presented to both eyes. To prevent participants from relying on local features to complete the task, the size of the fixation cross will be randomised across trials (sizes = 0.5 to 2.25 DVA in steps of 0.25 DVA) and jitter will be applied to both circles and to the fusion stimuli (jitter = 0.025 to −0.025 DVA in steps of 0.005 DVA, applied individually to x and y stimulus coordinates per trial). Foveal circles will always be presented surrounding the fixation cross (centrally plus positional jitter), while peripheral circles will be presented at a location that either surrounds the blind spot or is above the blind spot. For the peripheral location that surrounds the blind spot, circle stimuli will be situated centrally to the mapped blind spot location (plus positional jitter). To get the above location which does not surround the blind spot, a polar angle representing half the height of the blind spot plus the radius of the peripheral circle plus 2 DVA rotation of padding is added vertically to the centre of the blind spot.

Participants will complete a total of 50 adjustments (10 different start sizes: 5 larger than periphery, 5 smaller than periphery; each start size will be repeated 5 times) per eye and location (200 total adjustments) for each hemifield without a time constraint for responses. A full session of this task lasts approximately one hour.

Using this data, we will model the distribution of perceptual equivalence across trials, which will be allowed to vary in terms of bias and precision according to the experimental conditions (around vs not around the blind spot, ipsilateral vs contralateral eye), making it possible to quantify potential disruption of area perception induced by the blind spot.

### Experiment 3: Motion curvature task

See Fig 5 for an illustration of a single trial of this task. For each trial, we will present participants with an apparent motion trace that will either appear neighbouring the innermost side of the blind spot (“adjacent to blind spot” location), or at an eccentrically comparable location (“above blind spot” location). Each apparent motion trace will be composed of 1 dot (diameter = 1.4 DVA) appearing briefly at 4 positions, all equidistant to their immediate neighbouring position. The trace’s second and third dot-positions will be located at a fixed distance from fixation (defined for each participant depending on blind spot coordinates and size). By contrast, the trace’s first and fourth dot-positions will be respectively displaced from the second and third dot-positions along a trajectory that will be curved towards or away from fixation (curvature ranges = −0.4 to 0.4 DVA^-1^ in steps of 0.05 DVA^-1^). This will create the perception of a curved motion (apparent motion curvature). The motion trace will be repeated so that the dot is going away from its starting position, returning to it and going away from it again before disappearing. Each motion trace will be followed by a change of fixation from a ‘+’ to an ‘x’ to prompt a response, and the task will be to determine whether the motion trace was curved towards or away from fixation.

**Fig 5 pone.0340593.g005:**
[figure not shown]
Motion curvature task: All trials begin with the presentation of the blind spot shape and central cross until the fixation is maintained for at least 200 ms. We illustrate two given trials over time (t) in which a motion trace is A. presented around blind spot, appearing at locations 1 (darkest gray circle), 2, 3 and 4 (white circle; 100ms/location). Following this, the same motion trace is presented appearing at locations 4 (darkest gray circle), 3, 2, 1 (white circle; 100ms/location) before appearing again at locations 1, 2, 3 and 4 (100ms/location) and B. is presented above blind spot appearing at locations 1, 2, 3 and 4 (100ms/location). Following this, the same motion trace is presented appearing at locations 4 (darkest gray circle), 3, 2, 1 (white circle; 100ms/location) before appearing again at locations 1 (darkest gray circle), 2, 3 and 4 (white circle; 100ms/location). All trials end with a fixation stimulus change from ‘+’ to ‘x’ which cues for a response to the task. Participants’ task is to state whether that trial’s motion path was curved towards the left (towards the blind spot in the left hemifield, towards fixation in the right hemifield) or the right (towards the fixation in the left hemifield, towards the blind spot in the right hemifield). Note that while we represent the stimuli in black and white, the real task will be coloured and will be performed with the coloured glasses as shown in Fig 1A. This will allow us to present the stimuli at different locations to either the contralateral eye or ipsilateral eye.

The apparent motion curvature (i.e., the curvature by which the first and second dot-positions and the fourth and third dot-positions are displaced from one another) for a given trial will be determined by a staircase procedure: if the participant selects the motion trace as being curved towards fixation, the apparent curvature for the next trial in this staircase will be incremented in the opposite direction (less curved towards fixation/more curved away from it). Conversely, if the participant selects the motion trace as being curved away from fixation, the next apparent curvature will be incremented towards the fixation.

The exact locations of the motion traces (adjacent to and above blind spot) as well as the distance between the traces’ dot positions will be determined for each hemifield of each participant given their mapped blind spot area. For the adjacent to blind spot location, the second and third dot positions are above and below a point that connects the fixation cross with the centre of the mapped blind spot location. This point, on which the second and third dot positions are centred, is displaced from the centre of the blind spot by the participants’ blind spot size (blind spot width/2), the maximum width of the curved stimulus and padding (minimum = 0.5 DVA). The separation between the dots will be fixed at 2 DVA for all participants. The first and fourth dot positions will be displaced from the second and third by the curvature of a given trial (i.e., all dots will fall on a circle with radius = 1/curvature). All dots (1, 2, 3, 4) will be equidistant to their neighbours at all trials (distance1–2 = distance2–3 = distance3–4). The same procedure is used for the location above the blind spot except that a polar angle representing half the height of the blind spot plus 1.7° rotation of padding is added to the blind spot location.

Motion traces will be shown dichoptically to the ipsilateral or contralateral eye either adjacent to or above blind spot location. For each of these combinations, we will define 2 staircases, one for which the angle curvature starts as curved towards fixation (i.e., curvature = 0.4 for the right hemifield or curvature = −0.4 for the left hemifield) and one for which the angle curvature starts as curved away from fixation (i.e., curvature = −0.4 for the right hemifield or curvature = 0.4 for the left hemifield). This yields a total of 8 staircases that will run interlaced to compose one run. Each staircase procedure ends when it has lasted for at least 30 trials and 10 reversals.

Using this data, we will model psychometric functions relating apparent motion curvatures to the proportion of times they are chosen as being curved away from fixation. These functions will be allowed to vary in terms of bias and precision according to the experimental conditions (adjacent to vs above blind spot, ipsilateral vs contralateral eye), making it possible to quantify potential disruption of apparent motion perception induced by the blind spot.

### Data collection procedures

Participants will read and complete the information and consent forms using an anonymised subject ID. The participant will first complete the colour calibration and blind spot mapping tasks, which will follow the experimental procedure explained above. Then, the participant will take part in one of the three main experimental tasks (distance task or motion curvature task or area task). Each experimental task will follow the procedures outlined above. Since continuous fixation can be tiring, participants will be allowed to take a break whenever needed by asking the experimenter to call for a recalibration. Altogether, each experimental session is estimated to be completed in ~1h30 mins.

### Operational hypotheses

See Table 1 for a detailed description of each theories’ predictions. In this study protocol, participants will (i) compare the spatial separation between two dot-pairs (to compare distance), (ii) match the area of a circle relative to another (to estimate area size) and (iii) judge the curvature of apparent motion traces (to estimate apparent motion curvature) in trial-based psychophysics tasks. In all three paradigms we compare the accuracy (relating to bias) and precision (relating to slope) of responses to stimulation being presented near the blind spot location or at an eccentrically comparable location away from the blind spot (e.g., above), and for the ipsilateral and the contralateral eye.

**Table 1 pone.0340593.t001:** Table of experimental predictions.

Blind spot (ipsilateral) Predictions about the effect of stimulation around the blind spot on PSE (spatial bias)					
Theory	Decrease	No change	Increase	Confidence	Rationale
IIT	X			Medium	If there is less visual cortex in the blind spot area, it will feel like there’s less visual space in that region (for caveats cf. main text)
NREP	X	X		High	The distance between dots whose rectilinear connection goes through the blind spot, will be inferred by mechanisms using the through-blindspot line information (=incomplete) as well as using the around-blindspot trajectories. The overall estimate may be fully or incompletely corrected for the blind spot gap. Confidence is High that there is no change OR a modest decrease
AI		X		Medium	Perceptual inference reflects unbiased posterior estimate
Predictions about the effect of stimulation around the **blind spot** on **sensitivity (slope)**					
**Theory**	**Decrease**	**No change**	**Increase**	**Confidence**	**Rationale**
IIT	X			Medium	Extra-theoretical considerations suggest that variation in visual quality (btw. stimulated and filled-in qualities) may add to decision variability (a broader psychometric function)
NREP	X	X		Medium	The above ‘conflict’ between through-blindspot and around-blindspot trajectory information may decrease the sensitivity somewhat
AI	X			Medium	Precision estimates will be compromised by reduced information
**Blind spot (contralateral)** Predictions about the effect of stimulation around the **Corresponding Region of Contralateral Eye** on **PSE (spatial bias)**					
**Theory**	**Decrease**	**No change**	**Increase**	**Confidence**	**Rationale**
IIT	X			Low	Similar to ipsilateral rationale (visual space feels fused between L/R eyes – predictions differ to the extent that binoc. fusion fails)
NREP		X		Medium	Lack of information from contralateral field will not (or only slightly) affect distance estimation when dots are seen via ipsi (left) eye
AI		X		High	Perceptual inference reflects unbiased posterior estimate
Predictions about the effect of stimulation around the **Corresponding Region of Contralateral Eye** on **sensitivity (slope)**					
**Theory**	**Decrease**	**No change**	**Increase**	**Confidence**	**Rationale**
IIT		X		Medium	Extra-theoretical considerations suggest that similar visual quality may make for consistent stimulus comparisons
NREP		X		Medium	Lack of information in contralateral field will not (or only slightly) affect sensitivity of distance estimation when dots are seen via ipsi (left) eye
AI		X		Medium	Precision estimates will not be encumbered by any loss of information

Firstly, IIT proposed that differences in connectivity between monocular and binocular cortex may lead to a warping of visual space towards the blind spot region (i.e., a bias effect of the ipsilateral and contralateral eye for the blind spot location, Fig 6), causing space to be perceived as smaller when comparing spatial percepts that span – compared to those that do not span – the blind spot location. They further suggested that judgements could be more variable around the region of the perceptual blind spot (i.e., precision effect of the ipsilateral eye in the blind spot location, Fig 6). This second prediction resulted from considerations of Signal Detection Theory rather than IIT.

**Fig 6 pone.0340593.g006:**
[figure not shown]
Simulated data: Simulated data of the three theories with respect to experiment 2.a Simulated data of IIT, NREP and AI predictions with respect to the A. distance estimation task, B. area size task and C. motion curvature task. See Table 1 for a detailed description of these predictions. A sample of the code used to simulate the predicted data represented in the figures is available at: https://github.com/[name]/Intrepid_2a_staircase_simulation/tree/master.

By contrast, NREP posited that the internal models should largely compensate for most of these structural deviations, arguing that differences in judgement accuracy and precision would be ‘small’ (modestly significant) or ‘non-existent’ between blind-spot and non-blind spot regions (i.e., small bias and precision effects for the ipsilateral eye in the blind spot location, Fig 6). The reasoning behind this prediction is that the spatial judgement will be mostly determined by inferences based on the available sensory evidence gathered from around the blind spot, whereas the (incomplete) through-blind spot sensory inputs (including the border regions) can nonetheless weigh into the decision.

Lastly, AI argued that the internal models should compensate for the entirety of the cortical differences between the blind spot and its neighbouring regions, proposing that judgement accuracy around the blind spot location should be unaffected (i.e., no bias effect for either eye). However, AI posited that since internal models may have noisier predictions around the blind spot, judgements could be more variable (i.e., less precise) when spanning the blind spot, but that judgement accuracy should be unaffected.

### Planned analyses and expected outcomes

Using the data from task 1, we will model the psychometric functions relating the distance difference between target and foil to the proportion of trials the target is chosen as being the smaller distance. Using the data from task 2, we will model the distribution of perceptual area size equivalence across trials. Using the data from task 3, we will model the psychometric functions relating apparent motion curvatures to the proportion of times they are chosen as being curved away from fixation. The resulting models, fitted using a probit link function, will be allowed to vary in terms of intercept (capturing bias effects) and slope (capturing precision effects) according to the experimental conditions (around vs not around the blind spot, ipsilateral vs contralateral eye). Thus, our modelling approach will quantify the potential disruption of spatial perception induced by the blind spot as bias and precision effects for either the ipsilateral or contralateral eye. This modelling approach will be implemented in two ways. We initially use a linear mixed effects model (lme4 package in Rstudio; see [29]), which includes random intercepts for participant and hemifield in addition to the fixed effects of our experimental conditions. This has allowed us to get a first estimate of the effect of eye (ipsilateral eye vs contralateral eye) or location (nearing vs away from blind spot) on the bias and precision of spatial perception while accounting for participant and hemifield response variability.

In the final stage, once data collection is completed for all experiments in the adversarial collaboration, we will use the Bayesian approach outlined by [30]. This framework was specifically developed for the purposes of comparing alternative theoretical hypotheses in the setting of adversarial collaborations. Briefly, this method involves specifying a set of generative models, where each model is equipped with a theory-specific prior derived from the predictions declared in this protocol and the OSF preregistration. These models are then fitted to the observed data using variational Bayesian techniques to obtain an estimate of the (log) model evidence (i.e., marginal likelihood or evidence lower bound), which quantifies the probability of the observed data under each model ([31]). These quantities can then be compared to assess how much evidence each theory has accrued for its predictions. This model comparison procedure is applicable in the context of our data as well as in the context of the wider adversarial project, making it particularly appropriate in our setting. Crucially, there will be no difference in the basic results for our experiments for the two approaches – by specifying neutral priors, this modelling approach will recover the same general bias and precision effects as described above. However, the Bayesian approach goes beyond these basic results, providing relative weights that will favour some theories over others.

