### Predictive processing (AI, NREP)

Set within the general Predictive Processing framework, both Active Inference (AI) and Neurorepresentationalism (NREP) accounts are based on the assumption that perception relies on internal models that are optimised to reduce prediction errors, therefore working against perceptual distortions.

With respect to consciousness, AI claims that shifts in conscious perception require active inference, which refers to planning and decision-making in terms of inference of policies for action (such as decisions to shift attention, or engage in eye movement), where policies are inferred under the expectation they will reduce uncertainty about the hidden states of sensation ([6,7,12–14]). Uncertainty reduction equates to belief updating, which can be inferred through participants’ behaviour as a proxy of conscious perception. With respect to the physiological blind spot, AI proposes that the internal models compensate for structural deviations, arguing against perceptual distortions being associated with the physiological blind spot. However, given that internal models have noisier sampling in and around the blind spot region, AI predicts that judgements involving the blind spot should be more variable (i.e., no difference in terms of accuracy but less precision).

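### In tasks 1 and 3 bias is read from the probit intercept although the theories' predictions are on the PSE; when the PSE is not zero, a slope change alone moves the intercept.

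*Protocol article*

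**What the plan says.** Under Planned analyses and expected outcomes, the link is given: "The resulting models, fitted using a probit link function". The same sentence assigns the parameters, which "will be allowed to vary in terms of intercept (capturing bias effects) and slope (capturing precision effects"), according to location and eye. The first-stage mixed model is one "which includes random intercepts for participant and hemifield in addition to the fixed effects of our experimental conditions".

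Table 1, under Operational hypotheses, uses a different scale for bias. Its first block is headed "Predictions about the effect of stimulation around the blind spot on PSE (spatial bias"), and the contralateral block is also on the PSE. Sensitivity (slope) has its own blocks.

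The predictions that matter here are:
- **Active inference (AI):** PSE unchanged in both eyes, slope lower in the ipsilateral eye. The Introduction puts it as "no difference in terms of accuracy but less precision". The text after Fig 6 says "judgement accuracy around the blind spot location should be unaffected (i.e., no bias effect for either eye"). The rationale for the slope loss in Table 1 is "Precision estimates will be compromised by reduced information".
- **Integrated information theory (IIT):** PSE decrease in both eyes, slope decrease in the ipsilateral eye only.
- **Neurorepresentationalism (NREP):** ipsilateral PSE and slope each unchanged or decreased, with no change in the contralateral eye.

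For the final Bayesian stage the protocol says that, with neutral priors, "this modelling approach will recover the same general bias and precision effects as described above". The article nowhere defines bias as minus intercept over slope, or says that the stimulus variable is centred on a common PSE.

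**The concern.** The intercept measures bias in units of sigma, whereas the PSE measures it in stimulus units. If slope were the same in every condition, the choice would only rescale the answer. Here slope is expected to differ, and in the cell that separates the theories.

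Two patterns in Table 1 are exposed. AI's pattern (same PSE, lower slope) can produce an intercept difference that reads as a change in bias. IIT's pattern (equal PSE shift in both eyes, lower slope in one) would show a smaller intercept shift in the ipsilateral eye. That suggests an eye difference in bias that is absent on the PSE scale, and it understates the effect in the cell the experiment was designed to test.

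The Discussion describes a small NREP effect as one that is modest but reaches p < 0.05, so a modest artefact could be taken for a theoretically meaningful result.

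**Working it through.** **Inputs from the protocol.** Probit link, with intercept and slope varying by condition; 32 participants per experiment. In the distance task, x (foil minus target distance) runs from −3.5 to +3.5 DVA in steps of 0.5, with 8 staircases per run, each of at least 30 trials and 10 reversals. With 2 staircases per eye-by-location cell and two hemifield runs, this gives at least 2 × 30 × 2 = 120 trials per cell per participant, and 120 × 32 = 3,840 per cell in all. The protocol states no sigma, baseline PSE or power, so there is no figure of its own to reproduce.

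**Assumed, not in the protocol.** Sigma 1.5 DVA rising by a factor of 1.5, the same PSE in the two compared conditions, between-participant SD of PSE 0.5 DVA, and a two-sided 5% level.

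**Algebra.** If P(target chosen as smaller) = Φ((x − PSE)/σ) = Φ(a + b·x), then b = 1/σ, a = −PSE/σ and PSE = −a/b. With the PSE fixed and σ rising from σ₀ to σ₁, the intercept shift is −PSE/σ₁ + PSE/σ₀. This is zero only if PSE = 0, and otherwise moves the intercept toward zero.

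**Pure precision loss.** The table gives the algebraic shift for σ from 1.5 to 2.25. Beside it are rejection rates at 5% from simulated distance-task staircases, with 60 replicates per row. The intercept test is a probit regression with participant intercepts, a condition effect and a condition-by-x term. The PSE test is a Wilcoxon test on participants' differences in −a/b.

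| Mean PSE (DVA) | Intercept, σ 1.5 | Intercept, σ 2.25 | Shift | Intercept test rejects | PSE test rejects |
|---|---|---|---|---|---|
| 0 (no spread) | 0 | 0 | 0 | 2% | 2% |
| 0 | 0 | 0 | 0 | 7% | 8% |
| −0.25 | 0.167 | 0.111 | −0.056 | 38% | 2% |
| −0.5 | 0.333 | 0.222 | −0.111 | 80% | 10% |
| −1.0 | 0.667 | 0.444 | −0.222 | 100% | 3% |
| +0.5 | −0.333 | −0.222 | +0.111 | 73% | 5% |

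The slope effect was detected in every replicate. The typical estimated PSE difference stayed between −0.01 and +0.03 DVA. At PSE −0.5 the algebraic shift is −0.067 if sigma rises by 1.25 and −0.167 if it doubles.

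**A second set of assumptions.** Sigma is 1.0 in three cells and 1.4 in the ipsilateral blind-spot cell, with the same PSE in all four. At PSE 0.5 the intercept moves from −0.5/1.0 = −0.500 to −0.5/1.4 = −0.357. The intercept test rejected in 0%, 55% and 88% of 60 replicates at PSE 0, 0.25 and 0.5 DVA. The PSE test rejected in 2%, 3% and 7%.

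The Monte Carlo standard error is at most about 6 points, and about 3 points near a rate of 5%.

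**IIT's pattern.** Suppose the PSE is zero away from the blind spot and −d at it, in both eyes, and sigma rises by 1.5 in the ipsilateral eye only. The intercept shift is d/σ contralaterally and d/(1.5σ) ipsilaterally, which is one third smaller whatever d is. With d = 0.5 and σ = 1.5 the shifts are 0.333 and 0.222, although the PSE shifts are equal.

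**The case against.** **The artefact needs a non-zero PSE, and the protocol reports none.** This stands. At PSE 0 the intercept test keeps close to its nominal level. Table 1 also justifies AI's prediction by an unbiased estimate; read literally, that puts the PSE at physical equality, where the intercept stays at zero whatever the slope. A non-zero PSE is plausible, since a spanning target is compared with a foil above or below it and curvature is judged peripherally, but for AI's pattern it remains an assumption. IIT's own prediction supplies one.

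**The simulated offset fits part of task 1 poorly.** This also stands. When the target does not span the blind spot, target and foil are both off-axis, foil position and order are randomised, and staircases start from both extremes, so a PSE near zero is reasonable. An offset confined to the spanning location would still shift the ipsilateral-versus-contralateral intercept contrast there, by the same algebra, but the rejection rates above need not carry over to the full eye-by-location model.

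**A reader might extend the point to task 2.** The documents do not support that. Task 2 collects adjustment settings and models their distribution, and the centre of the settings is itself the equivalence point.

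**A reader might infer that AI would always be wrongly penalised in favour of a rival.** That goes too far. The spurious shift takes its sign from the baseline PSE, so it can mimic an increase that no theory predicts. The mixed model is described as a first estimate, and arbitration rests on Bayesian model evidence whose parameterisation the article leaves open.

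**The wording may be condensed.** An article may leave computation of the PSE to code, and the text does not prove that the PSE will go uncomputed. But it does more than omit a detail: it names the intercept as the bias measure, and that conflicts with Table 1.

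**Conclusion.** The point holds for the probit models of tasks 1 and 3. The parameter named for bias is not the quantity on which the theories declared their predictions, and the two part company where a slope change is expected. With a non-zero PSE, a pure precision loss can appear as a bias effect of either sign. An equal PSE shift in both eyes with lower ipsilateral slope would appear as an eye difference and understate the ipsilateral effect.

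The identity is exact; the size is conditional. Under the assumed sigmas, with an offset common to the compared conditions and N = 32, false bias findings run from about 5% at PSE 0 to roughly 40–55% at an absolute PSE of 0.25 DVA and 75–90% at 0.5 DVA. These rates are for the distance task. The algebra applies equally to task 3, whose stimulus scale is curvature, but no rates were computed for it. The documents do not support saying that every precision loss will register as bias.

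**What to change.** For tasks 1 and 3, define the bias effect as the condition contrast in PSE. Either of two routes will do:
- fit Φ((x − PSE)/σ) with condition effects on PSE and on log σ; or
- keep the mixed probit model, compute −intercept/slope for each eye-by-location cell, and report PSE contrasts with delta-method or participant-bootstrap intervals.

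State that the theory priors of the Bayesian models for these two tasks are placed on PSE and log σ, so that they match Table 1. For task 2, say that bias is the centre of the adjustment settings and precision their spread.

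The cost is analysis wording and code. No design change or new data are needed, and the protocol already provides for timestamped amendments in the OSF preregistration.
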